## Discussion

Post-COVID syndrome affects a significant proportion of the working population worldwide and there is as yet no specific causal therapy. Recovery also tends to be a long process, making it difficult to re-enter social and working life. However, data to date show that the course can be favourably influenced with multimodal symptom-oriented interventions [10, 11]. This leads to the task, especially for rehabilitation, of developing, providing and evaluating appropriate treatment concepts. The questions arise as to how suitable possibilities for easily accessible diagnosis and therapy of post-COVID can be created for post-COVID patients, what connections exist between post-COVID symptoms and other health problems that may also be present, and to what extent psychosomatic factors play a role in post-COVID symptoms. In particular, chronic fatigue, depression and anxiety, as well as cognitive problems, often occur and will be investigated in more detail in this multi-centre study with several rehabilitation clinics for different indications. As treatment programs for post-COVID are emerging, it seems particularly relevant to examine the impact of the various interventions currently offered to post-COVID patients on post-COVID symptoms. It needs to be clarified whether in some cases additional neurological, psychosomatic or internal rehabilitation treatment in a suitable clinic is required and, if so, how frequent such cases are. In order to ensure the best possible care, an answer to the question of whether indications of particularly suitable therapy offers can be found on the basis of the patients’ current findings and their medical history would be important.

As post-COVID symptoms and especially post-COVID fatigue often appear to have profound effects on daily functioning, including work ability and quality of life, significant economic impacts are also expected through increased sick leave and use of health care, as is already the case for patients with infectious diseases other than COVID-19 [42, 43]. Given the global scale of this pandemic and the large group of potential patients, special attention must be paid to how society as a whole will be affected.

### Strength and limitations

Following the recommendation of the research agenda for post-COVID fatigue [13], this study uses largely internationally established and previously validated instruments to measure fatigue and other post-COVID symptoms. The strengths of this study include the large sample size and the nationwide distribution of the cooperating rehabilitation centres, which thus also reflects regional differences and characteristics of the various rehabilitation indications. The inclusion of different therapy focuses per indication with different intensity and duration of treatment is on the one hand a weakness of the study, as no uniformly defined intervention can be depicted, but on the other hand it reflects the reality of healthcare. This improves the external validity of our study results. The resulting comparison between the different care structures also enables care research to be conducted within this study. We assume that within the framework of this observational study, statements can be made reliably about which and how much therapy the respective patient groups need. With this approach, the treatment of the control group resembles usual care and offers the possibility to make statements about whether pure post-COVID diagnostics might be sufficient for certain patient groups.

However, external validity outside Germany will be limited due to differences in health care systems. A further relevant weakness is that there is no RCT design, but this is difficult for ethical and legal reasons, first because in Germany everyone has a legal right to rehabilitation (entitlement to rehabilitation) and second because rehabilitation is relevant to clarify the socio-medical situation.

## Conclusion

This protocol describes a multi-centre, non-randomised, controlled longitudinal study, plus multi-group comparisons, which will take place in seven rehabilitation clinics of different specialisations. By providing a detailed diagnosis of post-COVID symptoms and an indicative treatment tailored to the special needs of post-COVID patients, this study aims to determine the respective needs of symptomatically different affected persons for treatment options, to answer the question of which patient groups need which doses of treatment and which interventions, and at which points modifications should be made in the treatment concepts in order to ensure an optimal therapy. Referring to the high prevalence of post-COVID syndrome [2], their large burden of disease [5, 10] and economic impact on labour markets and social security systems [7, 8], a positive evaluation of the intervention, detection of possible adverse events and subsequent implementation into practice could be of large mental and public health and economic relevance.

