#### Interventions

Depending on the symptom focus, rehabilitation patients with post-COVID are treated in specialized rehabilitation clinics. The clinics and their treatment programs are listed below (Table 1). Since post-COVID syndrome is a new clinical picture with multi-organ involvement, attempts are currently being made to assign patients to already existing rehabilitation structures according to symptom focus. As can be seen, the specialisations diverge in the duration and frequency of the therapies, but uniformly cover all essential symptom areas of the post-COVID syndrome with corresponding offers (psychoeducation, exercise, psychotherapy, breathing and relaxation therapy, cognitive training).

**Table 1 Tab1:** Interventions

Clinic	Psychoeducation	Exercise therapy /physical therapy	Relaxation	Psychotherapy		Respiratory therapy	Cognitive training	Creative therapy	Other
				Group	Single session				
*Rehabilitation Centre Todtmoos*									
Pneumological departement	1 × per rehabilitation/60 min *Post-COVID Pneumology* 1 × per rehabilitation/90 min *Post-COVID psychosomatic perspective* 1 × per rehabilitation/60 min *Introduction to exercise therapy*	3 × per week/30 min exercise therapy 5 × per week/30 min monitored ergometer training	3 × per week/30 min relaxation therapy 1 × per week/60 min QiGong (as needed)	2 × per rehabilitation/90 min	1 × per rehabilitation/45 min	4 × per week/30 min	As needed (Freshminder)	Ergotherapy (as needed) Art therapy (as needed)	1 × per week/60 min pacing-group Olfactory training (as needed) Nutrition advice (as needed) Social service (as needed)
Psychosomatic Department		1 × per week/90 min exercise therapy 4 × per week/30 min monitored ergometer training	2 × per week/30 min relaxation therapy	2 × per week/90 min 1 × per week/60 min	1 × per week/30 min	2 × per week/30 min		1 × per week/90 min Ergotherapy 1 × per week/90 min Art therapy	
Psycho-pneumological departement		2 × per week/60 min exercise therapy 4 × per week/30 min monitored ergometer training	2 × per week/30 min relaxation therapy	3 × per week/90 min	1 × per week/60 min	5 × per week/30 min		1 × per week/90 min Ergotherapy	
*Alpcura Clinic*									

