The rehabilitation concepts of the neurological clinics are so individual that it is not possible to make any useful and schematic statements about therapy times in advance

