### Data management and analysis

#### Data management

Outcomes and other measures will be assessed with patient questionnaires and cognitive assessment, with medical examination and somatic assessment (see Fig. 2) or will be extracted from the rehabilitation discharge letters (e.g. primary and demographic data; socio-medical parameters e.g. employment, current sickness absence, sick leave duration in weeks, ability to work on admission and discharge). For participants who do not complete follow-up questionnaires, missing data will be imputed. If participants withdraw their participation, the collected data will be deleted. The patient data are stored anonymously in a electronic study-data file with a patient cipher, whereby the paper–pencil data are entered manually. Paper-pencil questionnaires will be stored in locked filing cabinets and electronic data will be stored on secured servers. To assure a safe and secure environment for data acquired, data transmission is encrypted with secure socket layer (SSL) technology.

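### The article claims it can say reliably which patients need which dose of therapy, but it names no measure or analysis of therapy received, and planned dose cannot be separated from programme and case mix

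*Protocol article*

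**What the plan says.** Two places in the protocol article make the claim. The Conclusion gives as an aim to answer "which patient groups need which doses of treatment and which interventions". Strength and limitations assumes that, within this observational study, "statements can be made reliably about which and how much therapy the respective patient groups need".

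The same section concedes that "no uniformly defined intervention can be depicted" and that the study is not randomised. Under Interventions the article notes that "the specialisations diverge in the duration and frequency of the therapies". It also explains how patients come to a programme: "attempts are currently being made to assign patients to already existing rehabilitation structures according to symptom focus". The note to Table 1 says of the neurological clinics that "it is not possible to make any useful and schematic statements about therapy times in advance".

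On data, Table 2 lists psychological, neurological and somatic assessments and adverse-event recording. Data management adds items that "will be extracted from the rehabilitation discharge letters", with demographic and socio-medical examples. Study variables adds a retrospective record, at the six-month follow-up, of further medical measures. On analysis, Treatment effect compares the rehabilitation clinics with the outpatient control group. Its subgroups are defined by symptom characteristics and comorbidity.

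**The concern.** A claim about how much therapy a group needs requires three things: a record of how much each patient received, variation in that amount that is not simply a marker of who the patient is, and an analysis relating amount to outcome. The article names neither the record nor the analysis, and what it says about allocation tells against the variation being usable.

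What is at stake is the conclusion. The article expects its results to feed into treatment concepts and implementation. If one programme does better than another and also schedules more minutes of some therapy, the present wording invites the reader to credit the minutes. The difference could equally come from the rest of the programme, from the clinic, or from the kind of patient sent there.

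**Working it through.** The article gives no figure for dose, so there is none to reproduce. The check has two parts.

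**1. Does any named element carry dose?**

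| Place in the article | Content | Therapy received or dose named? |
|---|---|---|
| Research questions | Symptoms, change, settings, prognosis, illness behaviour, adverse events | No; 2.2 asks about settings only |
| Study variables | Tests at admission and discharge; further measures recorded at follow-up | Not described as therapy delivered in rehabilitation |
| Table 2 | Assessments and adverse events | No |
| Data management | Discharge-letter items, given as open examples | Not named |
| Treatment effect | Clinics against control; patient-characteristic subgroups | No dose or therapy-type term |

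**2. Can planned dose from Table 1 stand in?**

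Scheduled minutes per week were built from Table 1 as sessions × minutes. Items given only as needed, items stated per rehabilitation stay, and items without minutes were left out. Where a programme offers alternatives, the first was used.

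| Programme | Exercise (min/week) | Respiratory (min/week) |
|---|---|---|
| Todtmoos, pneumological | 3×30 + 5×30 = 240 | 4×30 = 120 |
| Todtmoos, psychosomatic | 90 + 4×30 = 210 | 2×30 = 60 |
| Todtmoos, psycho-pneumological | 2×60 + 4×30 = 240 | 5×30 = 150 |
| Alpcura, low capability | 3×(2×30) = 180 | 2×45 = 90 |
| Alpcura, higher capability | 180 + 45 + 45 = 270 | 2×45 = 90 |
| Seehof, psycho-cardiological | 2×30 + 2×30 = 120 | 2×30 = 60 |
| Gelderland, psychosomatic | 45 + 45 + 60 = 150 | 2×30 = 60 |

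The two neurological entries are excluded. Neither gives a frequency or duration for exercise. One states only an overall 19–21 sessions per week, not split by therapy type.

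Identifiability, by matrix rank:

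- Four clinic indicators have rank 4. Adding planned exercise or respiratory minutes raises it to 5, so planned dose is not fully aliased with clinic.
- Seven programme indicators have rank 7. Adding either dose leaves it at 7, so planned dose is fully aliased with programme. The number of contrasts is 7 − 1 = 6.

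Where the variation lies (programmes weighted equally; between-clinic share = 1 − within-clinic sum of squares / total sum of squares):

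- Exercise: mean 1410/7 = 201.4 and total 17,485.7. Within Todtmoos (mean 230): 100 + 400 + 100 = 600. Within Alpcura (mean 225): 2,025 + 2,025 = 4,050. Share = 1 − 4,650/17,485.7 = 0.73.
- Respiratory: mean 630/7 = 90 and total 7,200. Within Todtmoos (mean 110): 100 + 2,500 + 1,600 = 4,200. Within Alpcura: 0. Share = 1 − 4,200/7,200 = 0.42.

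The within-clinic remainder is therefore not free variation. For exercise, 4,050/4,650 = 87% of it lies between strata defined by patient capability, and the rest lies between Todtmoos departments. For respiratory therapy all of it lies between those departments. In both cases the amount scheduled follows the type of patient.

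**The case against.** The strongest reply is that this is a matter of phrasing in an exploratory study. No numbered research question asks about dose, no dose test is planned, and Strength and limitations openly describes an observational comparison of care structures without a uniform intervention or randomisation. The text is also a condensed article. Table 2 is a list of assessments, where a therapy log would not be expected, and the discharge-letter list is open-ended.

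Much of this stands, and it rules out several stronger readings that a reader might infer:

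- That therapy received is not measured at all, or that patient-level dose information is zero. The documents support only that no such variable is named; a fuller protocol could contain one.
- That planned dose is aliased with clinic, or that all patients in a unit are scheduled the same. Todtmoos runs three departments, including the "Psycho-pneumological departement", with different schedules. Alpcura has two capability strata, and the neurological plans are individual.
- That the neurological entries say nothing about amount. One gives an overall number of sessions.

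The reply does not rescue the claim itself. The admitted limitations never say that the amount of therapy moves with case mix, and the text asserts reliability alongside them. The absence of a dose question or dose analysis widens the gap between the claim and the plan. A complete therapy record would not close it either: where therapy is given as needed, by individual plan or by capability, the amount received follows the patient's condition, so dose stays confounded by indication.

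**Conclusion.** The concern holds in this form: the article claims a property that the design it describes does not have. It says that dose needs can be stated reliably, while naming no therapy-received variable, no dose question and no dose term. The planned schedules offer at most six contrasts across seven programmes. All six coincide with programme contrasts, and programme follows symptom focus or capability. The neurological programmes cannot enter such a comparison by therapy type.

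The count of seven rests on reading the Alpcura strata and Todtmoos departments as separate programmes and on using scheduled weekly items only. The variance shares depend on those choices and on equal weighting of programmes. The aliasing does not: any dose fixed by programme is aliased with programme. The comparison between settings in question 2.2 is not affected by this point, although it remains non-randomised.

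**What to change.** In Strength and limitations, remove the statement that the type and amount of therapy needed can be determined reliably. In the Conclusion, remove the dose aim. Replace both with a statement that the study will describe how outcomes differ between care settings (question 2.2), and that the amount of therapy cannot be separated from programme and patient selection. This costs only a more modest claim.

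If the authors wish to keep an interest in dose, they could name therapy received as a study variable (sessions and minutes per therapy category and patient) and extract it at discharge. They would then analyse it within programme, adjusted for severity at t0, and report it as exploratory and subject to confounding by indication. This adds a few extraction fields. It assumes that the discharge records hold sessions and minutes, which the article does not say. It would remove the aliasing with programme but would not justify a claim of reliability.

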## Data Availability

Since the data that will be used in the targeted study in the future will be data on insured persons of the German Pension Insurance and strict data protection exists, these data are not publicly accessible, but can be made available by the corresponding author in a form adjusted for personal data upon justified request.

## Abbreviations

6MWT: Six-minute walk test
AEQ/AE-FS: Avoidance endurance questionnaire
ECG: Echocardiography
FSMC: Fatigue scale for motor functioning and cognition
LK-18: Life skills
MoCA: Montreal cognitive assessment
PHQ: Personal health questionnaire
PoCoRe: Post COVID rehabilitation
ReCoRD: Regensburger COVID recovery documentation
TAP: Test battery for attention
WAI: Work ability index
WHO-DAS 2.0: Disability assessment
